**Figure 1 f1:**
[figure not shown]
Flow chart of patient recruitment and study implementation.

The study used a simple randomization method. The steps are as follows: first, in Excel, we used the RAND function to generate a number between 0 and 1. The function is invoked by entering “=RAND()” in any cell and pressing Enter. The generated number determines the group assignment for each patient: if the number is from 0 to 0.5 (excluding 0.5), the patient is assigned to the intervention group; if it is from 0.5 to 1 (excluding 0.5), the patient is assigned to the control group. If the number is exactly 0.5, the process is repeated until a valid random number is obtained.

The blinded method used in this study involves several categories of individuals:

Medical staff in the research department (blinded): responsible for patient recruitment, informing patients of admission and follow-up times and locations, and conducting basic biochemical and imaging examinations for admission and follow-up, they are unaware of patient group assignments.Investigators (blind): Their responsibilities are strictly limited to one-on-one data collection with patients; they do not participate in other research activities to ensure data specificity and accuracy. Investigators are unaware of patient group assignments.Data processing personnel (blind): They receive coded data (Group A/Group B) and are unaware of the specific assignment relationship between Groups A/B and the intervention or control groups.Patients (unblinded): The intervention group is guided by the researcher to follow the Artificial Intelligence-Empowered Mobile Health Official Account and instructed on its use. The control group does not receive this service.System administrator (unblinded): Responsible for online management and answering questions for patients in the intervention group; their service is limited to patients in the intervention group, as only this group receives the Artificial Intelligence-Empowered Mobile Health intervention.

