**Specific Methods:**

Artificial Intelligence-Empowered Mobile Health provides patients who lack emotional outlets with humanized emotional release and real-time companionship support, filling the gap left by their reluctance to express themselves or insufficient family support.Artificial Intelligence-Empowered Mobile Health can provide recommendations for activities of interest and help patients plan their schedules, helping them avoid lying in bed alone, alleviating negative emotions, and solving their difficulties in choosing activities.Artificial Intelligence-Empowered Mobile Health solutions use human-like imagery and interactive entertainment features to provide alternative emotional support for patients living alone or lacking family support.Strengthen the connection between patients and researchers to identify serious issues and initiate timely medical interventions. Inform patients of follow-up appointment times, locations, procedures, required materials, and preparation requirements, such as fasting or holding urine.

**Phase 3: Follow-up to ongoing treatment**.

**Swanson’s Theory of Caring:** Knowing.

**Intervention providers:** Attending doctor, researcher.

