**Specific Methods:**

Conduct inquisition, physical examinations, and necessary auxiliary examinations, and promptly provide feedback and explanations of the results to patients.Collect patient responses and impressions regarding the use of Artificial Intelligence-Empowered Mobile Health through semi-structured interviews, and guide completion of follow-up questionnaires.

**Swanson’s Theory of Caring:** Doing for, Enabling.

**Intervention providers:** Researcher.

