**Specific Methods:**

Contact the patient proactively before the follow-up examination to reconfirm the time, location, and examination items.Accompany the patient throughout the follow-up examination on the day of the appointment, explaining the environment and the purpose of each examination to alleviate any feelings of unfamiliarity.Pay attention to the patient’s emotions, provide patient companionship and positive support, and encourage them to face the future with optimism.

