The Posttraumatic Stress Disorder (PTSD) Checklist for DSM-5 (PCL-5) is used to measure symptoms that meet the criteria of the DSM-5. The scale consists of four dimensions: intrusive symptoms, avoidance, cognitive/emotional negative changes, and hyperarousal, with a total of 20 items. Each item is scored on a scale of 0 to 4 (0 = “not at all” to 4 = “extremely “). The total score range is 0–80 points, with higher scores indicating more severe PTSD symptoms and greater functional impairment. The overall Cronbach’s alpha for the original scale was 0.94 (41).

Quality of life is measured using the EuroQol Visual Analogue Scale (EQ-VAS), which is used to assess the overall health status of participants. The EQ-VAS is a vertical scale on which respondents record their self-rated health status (42). The scale ranges from 0 to 100, with 0 representing “the worst health state you can imagine” and 100 representing “the best health state you can imagine”.

Physiological and biochemical data: Professional medical staff at the Inner Mongolia Maternity and Child Health Care Hospital, who are qualified to perform such procedures, strictly adhere to clinical operating procedures and hospital testing standards to conduct human chorionic gonadotropin (HCG) level measurements and ultrasound examinations on patients. The HCG level measurement employs chemiluminescence immunoassay, utilizing the advanced, fully automated chemiluminescence immunoassay analyzer to precisely quantify the level of human chorionic gonadotropin in serum. Ultrasound examinations are conducted using a color Doppler ultrasound diagnostic instrument, with experienced ultrasound specialists conducting detailed examinations and assessments of uterine morphology, endometrial thickness, and the presence of any residual material within the uterine cavity.

Qualitative interview: Researchers initially developed a semi-structured interview outline based on the research objectives and a review of relevant literature. After consulting with qualitative research experts and conducting preliminary interviews, the research team revised the interview outline based on expert discussions and finalized the content of the interview outline. During the interviews, researchers needed to maintain a certain degree of openness and flexibility. The outline included, but was not limited to, the following questions:

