What specific functionalities of Artificial Intelligence-Empowered Mobile Health did you use?Which Artificial Intelligence-Empowered Mobile Health functionalities had a positive effect on your health, and which ones had no effect or even had a negative effect?How did using Artificial Intelligence-Empowered Mobile Health affect your mental health? What do you think caused these effects?With the help of Artificial Intelligence-Empowered Mobile Health, what did you learn about post-abortion care?To what extent did you trust the health information provided by Artificial Intelligence-Empowered Mobile Health? Did you find its responses reliable? Why?’How did you feel when Artificial Intelligence-Empowered Mobile Health attempted to comfort or encourage you? Do you perceive this emotional support as genuine? Please elaborate on your feelings.”What were your expectations of Artificial Intelligence-Empowered Mobile Health prior to using it? How did its actual performance differ from your expectations?’Compared to support provided by healthcare professionals or family/friends, what unique aspects did you find in interacting with Artificial Intelligence-Empowered Mobile Health? Which form of support do you prefer? Why?’

Patient demographic information will be collected through the case system and self-designed questionnaires. (**Table 1**).

**Table 1 T1:** Variables and measures collected at every time point.

Variables	Date source	Measures	Baseline(T0)	Post-intervention(T1)
Intervention preparation	/	Eligibility screen, Informed consent and Allocation	✓	
Covariates	Baseline questionnaire	Sociodemographic information	✓	
	Baseline questionnaire and Follow-up questionnaire	Behavioral information	✓	✓
Primary outcome	Baseline questionnaire and Follow-up questionnaire	Patient Health Questionnaire-9 (PHQ-9)	✓	✓
Secondary outcome	Baseline questionnaire and Follow-up questionnaire	Generalized Anxiety Disorder-3, GAD-3	✓	✓
		Perceived Stress Scale 4, PSS-4	✓	✓
		Perceived Social Support Scale Short Form, PSSS-SF	✓	✓
		Body Image-Acceptance and Action Questionnaire-5, BI-AAQ-5	✓	✓
		Posttraumatic Stress Disorder Checklist for DSM-5, PCL-5	✓	✓
		EuroQol Visual Analogue Scale, EQ-VAS	✓	✓
	Clinical examination and laboratory tests	Ultrasound, human chorionic gonadotrophin, HCG		✓
Qualitative results	semi-structured interviews	Effect of the trial		✓

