The Data Monitoring Committee (DMC) consists of at least two members of the Ethics Committee of the Inner Mongolia Maternal and Child Health Hospital, who have no conflict of interest with the study. The DMC is responsible for conducting regular monitoring independently of the principal investigator and reporting to the Ethics Committee. It has the authority to suspend or terminate any study that deviates from the protocol. The Ethics Committee reviews the progress of the study and compliance with the protocol every six months. The research team must immediately report any serious adverse events (SAEs) or adverse events (AEs). If a participant experiences a serious adverse event, researchers must report it within 24 hours and halt the trial. In the event of a severe error in the intelligent agent or significant interaction issues, the trial must also be immediately suspended. The study may resume only after technical repairs and interface improvements have been confirmed. A pre-trial validation of the intelligent agent’s performance is conducted prior to study initiation, and all investigators undergo rigorous training and certification. In a standardized environment, investigators guide participants one-on-one to scan a QR code and complete a unified electronic questionnaire, explaining questions without prompting answers. Prior to the interview, participants are fully informed of the purpose, right to withdraw, and confidentiality measures. After obtaining signed informed consent, the interview is recorded and conducted in a private setting at the pre-agreed time. During the interview, investigators flexibly guide the conversation, listen attentively, and avoid subjective evaluations. In this study, we will utilize the “Wenjuanxing” (Questionnaire Star) online survey platform for questionnaire completion to ensure data accuracy. Before data analysis, we will conduct strict data organization and cleaning.

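### The protocol contradicts itself on who conducts the acceptability interviews; on one reading it is the role that delivered the intervention, which puts objective 2 at risk of social-desirability bias

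*Protocol article*

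**What the plan says.** Four places in the protocol article bear on who interviews.

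- **Section 2.5.4, Phase 3, the block under Knowing.** The intervention providers are "Attending doctor, researcher". The methods in that block include the instruction to "Collect patient responses and impressions regarding the use of Artificial Intelligence-Empowered Mobile Health through semi-structured interviews", and the same sentence continues with "guide completion of follow-up questionnaires".
- **Section 2.6.2.1, qualitative interview paragraph.** "During the interviews, researchers needed to maintain a certain degree of openness and flexibility".
- **Section 2.9, Study management.** "During the interview, investigators flexibly guide the conversation, listen attentively, and avoid subjective evaluations". The setting is private and the time agreed beforehand. The purpose, the right to withdraw and confidentiality are explained first.
- **Section 2.1, blinding list.** Investigators are unaware of allocation, and "Their responsibilities are strictly limited to one-on-one data collection with patients; they do not participate in other research activities".

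The interview outline in section 2.6.2.1 asks about trust in the information, whether the emotional support seemed genuine and how performance compared with expectations. It also asks for a comparison with healthcare professionals or family and friends, ending in "Which form of support do you prefer". It asks too which functions had no effect or a negative one. Acceptability is the second of the two specific objectives at the end of the Background. Table 1 contains no acceptability instrument.

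**The concern.** An acceptability interview is only as candid as the relationship between the woman and the person asking. In section 2.5.4 the researcher role demonstrates the service one to one, sends guidance every day, reviews the woman's conversations with the agent and shares the one-week contact with the attending doctor. At follow-up the researcher is told to "Accompany the patient throughout the follow-up examination on the day of the appointment". Section 2.8 adds a deliberate effort to build strong relationships with participants. If that role also asks whether the service was trusted and its comfort believed, some women may soften or withhold criticism.

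What is at stake is the answer to objective 2, including reports of unhelpful or harmful exchanges with a new AI agent. Those are among the most useful things the interviews could bring out.

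**Working it through.** No figure in the plan depends on this point, so there is nothing to recompute. The check is a comparison of role assignments.

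**Step 1. Who interviews?**

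| Section | Interviewer named or implied | Part in delivery? |
|---|---|---|
| 2.5.4, Phase 3 | Attending doctor, researcher (listed as intervention providers) | Yes |
| 2.6.2.1 | Researchers | Yes, if the term means the same role as in 2.5.4 |
| 2.9 | Investigators | No, if the term means the same role as in 2.1 |
| 2.1 | Investigators: blinded, data collection only | No |

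Two places point to the delivering role and one, read with the blinding list, points away from it. No sentence reconciles them.

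**Step 2. Which provider had which contact?** The provider lines in 2.5.4 give the demonstration of the service, the daily messages and the accompaniment at follow-up to the researcher alone. The introduction to the study and the one-week contact are shared with the attending doctor. The close daily relationship is therefore the researcher's. The doctor's position is that of the treating clinician.

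**Step 3. Does another measure carry objective 2?** Table 1 lists psychological scales, a quality-of-life scale, ultrasound and HCG, plus the interviews at T1. None of the listed instruments measures acceptability. Use of the system is reviewed (sections 2.5.3, 2.5.4 and 2.8), but for content updating, detection of problems and compliance, not as an acceptability outcome. The interviews are the main listed source.

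**Step 4. Does choosing section 2.9 settle it?** Not by itself. Every question in the outline is about the AI service, so an investigator who asks them learns the woman's arm. That conflicts with the unqualified blinding statement in 2.1. If the interview came before the T1 questionnaires, that investigator would then be collecting the self-reported outcomes unblinded. The order of interview and questionnaires therefore has to be fixed together with the role.

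**Step 5. Which way would bias run?** Courtesy towards the person who delivered the service would favour the service on trust, on genuineness of comfort and on reported harms. On the preference question, courtesy towards a healthcare professional could favour professionals over the AI. The comparator there also includes family and friends. The net direction is probably favourable to the service, but this is a judgement.

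**The case against.** The strongest reply is that the article already contains safeguards and that the Phase 3 block is loosely written.

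- The outline openly invites negative answers. Section 2.9 provides a private setting, explained confidentiality and neutral conduct. This stands as mitigation. It does not remove the difficulty if the person in the private room is the provider.
- Section 2.4.2 gives the interviews their own selection, consent and scheduled time. A reader might infer from Phase 3 that the interview takes place on the day the researcher accompanies the woman. The documents do not establish that.
- Researcher may be a generic label. The text does not say that the interviewer is the same individual who delivered that woman's intervention, nor that the attending doctor personally interviews. This also stands: the conflict is between roles, not named individuals.
- A condensed article may leave interviewer independence to the full protocol. That would answer a mere omission. Here the article does state the interviewer, in several places, and the statements disagree.

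It can also be argued that the wording on follow-up questionnaires in the same Phase 3 sentence is the weightier issue, because it bears on the PHQ-9. That is a separate matter and does not weaken this one.

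**Conclusion.** The contradiction over the interviewer is real and bears on objective 2. If Phase 3 is followed, acceptability is exposed to social-desirability bias of unknown size, probably favourable to the service overall. This assumes that researcher means the same role throughout section 2.5.4 and in 2.6.2.1, and that investigator means the same role in 2.1 and 2.9.

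A reader might go further and infer that providers are definitely assigned the interviews, or that their answers will inflate acceptability. The documents do not support either. Sections 2.1 and 2.9 point to a non-delivering interviewer, the preference question could be pulled the other way, and no figure allows the bias to be sized. The point does not touch the randomised comparison on the primary outcome. It is a cheap improvement that should be made, not a threat to the trial's main result.

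**What to change.** - In section 2.5.4, Phase 3, take the semi-structured interview out of the provider tasks.
- In sections 2.1, 2.5.4, 2.6.2.1 and 2.9, name one interviewer role in the same words: existing investigators who take no part in delivery, with no provider present.
- State that the interview is held only after that woman's T1 questionnaires have been submitted.
- Qualify the blinding statement in section 2.1: investigators are unaware of a participant's allocation until her T1 questionnaires are submitted, and may learn it at the interview.

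The cost is some investigator time and a few sentences of text; no new staff are needed. The downside is that the interviewer learns the arm of a woman whose questionnaire outcomes are already complete. Because section 2.4.2 already provides for separately scheduled interview times, the sequencing should be workable.

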**Intervention content:**

Artificial Intelligence-Empowered Mobile Health provides patients with a continuous interaction period of three months.Artificial Intelligence-Empowered Mobile Health offers long-term care knowledge after abortion.

**Specific Methods:**

On the day of the follow-up examination, the doctor will provide face-to-face guidance on key points for long-term post-operative care.Patients will be instructed that they can consult on authoritative social media platforms if they encounter any issues.

**Swanson’s Theory of Caring:** Being with, Maintaining belief.

**Intervention providers:** Researcher.

**Intervention content:**

Researchers provide accompaniment and guidance to patients during follow-up appointments.

**Specific Methods:**

Contact the patient proactively before the follow-up examination to reconfirm the time, location, and examination items.Accompany the patient throughout the follow-up examination on the day of the appointment, explaining the environment and the purpose of each examination to alleviate any feelings of unfamiliarity.Pay attention to the patient’s emotions, provide patient companionship and positive support, and encourage them to face the future with optimism.

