Abortion costs affect individuals, the healthcare system, and society. It is estimated that the short-term economic loss caused by abortion in the UK each year amounts to £471 million (4). Complications arising from unsafe abortions require a higher level of care (12), which not only increases treatment costs, leading to financial losses for individuals and consumption of medical resources (13), but also causes labor losses (14). In addition, abortion bans in some countries and regions will increase public expenditure, such as medical subsidies (15).

Current attention to psychological distress after abortion is insufficient. Routine intervention relies heavily on medical staff to provide preoperative explanations, post-operative structured counselling (16), and partner support or mutual-help groups (17). However, such medical resources are severely lacking in remote and underdeveloped areas. Some patients refuse post-operative follow-up due to financial constraints, resulting in their inability to accept structured psychological counselling. Current intervention methods require advanced planning and are conducted at fixed times and locations. However, the emotional distress is often sudden and unpredictable, making it difficult for traditional offline interventions to provide immediate emotional support, which may exacerbate the condition. Developing online intervention methods can compensate for the aforementioned shortcomings, but research in this field remains largely unexplored. Wang et al. developed an online short-term intervention for patients who had undergone abortions based on stress coping theory, which improved psychological well-being by enhancing self-efficacy and social support. The results showed that two weeks after the abortion, the intervention group had significantly lower depression scores, improved problem-coping abilities, and held more positive perceptions of their abortion experiences (18).

Mobile health is “medical and public health practices supported by mobile devices, such as mobile phones, patient monitoring devices, personal digital assistants (PDAs), and other wireless devices.” (19) The application of mobile health in medicine is becoming increasingly widespread. Its main advantages are that it can break through the limitations of time and space, is inexpensive to use, and can provide fast, rich, and personalized medical information (20).

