### Sample size

2.3

This study is a mixed-methods research. The intervention group will receive Artificial Intelligence-Empowered Mobile Health interventions, while the control group will receive standard care. Based on previous research findings, nursing interventions based on Swanson’s Theory of Caring have been shown to significantly reduce depression and anxiety levels in women who have experienced abortion, and can serve as a reference for effect size (29). The Minimum Clinically Important Difference (MCID) was selected as a reduction of ≥5 points on the Patient Health Questionnaire-9 (PHQ-9), which is considered clinically meaningful (30). The standard deviation (SD) is based on previous studies showing that the SD of PHQ-9 in the abortion population is approximately 6–8 points. The test level α = 0.05 and test efficacy 1-β = 0.90 are set, and according to the randomized controlled trial mean comparison formula:

$$n=\frac{{\left(Z_{\alpha /2}+Z_{\beta }\right)}^{2}\cdot 2\sigma^{2}}{\Delta^{2}}$$

The sample sizes for each experimental group are equal. Z_α/2_ = 1.96, Z_β_ = 1.28, σ = 8, Δ = 5 in this example. The sample size for each group can be calculated as n = 42 people. Considering the follow-up missing rate, the sample size for each group is increased to 50 people, for a total of 100 people.

Qualitative research is guided by the principle of information saturation, meaning that interviews with patients are stopped once a certain number of participants have been reached and no new information is emerging. Therefore, this study does not specify a minimum sample size for qualitative research.

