### Statistical analysis

2.7

After the trial is completed, all collected case data and questionnaire responses will be organized and summarized. Data storage will be managed using Microsoft Office 2017, while statistical analysis will be conducted using SPSS Statistics 27.0 software. Count data will be presented as case numbers (N) and percentages (%). The normality of continuous data will be assessed; normally distributed data will be presented as mean ± standard deviation, while non-normally distributed data will be presented as median (interquartile range) and interquartile range (P25-P75). Appropriate statistical tests (e.g., independent samples t-test, Mann-Whitney U test, and chi-square test) will be used to compare baseline characteristics between the intervention and control groups based on data type. Longitudinal analysis of follow-up data will be conducted using generalized estimating equations (GEE) to compare differences in outcomes between the two groups. Two-sided tests will be used, with statistical significance set at p < 0.05. In cases of missing data, multiple imputation techniques will be applied, considering the randomness of missing data. Multiple imputation involves generating multiple complete datasets by replacing missing values with reasonable estimates derived from observed data and imputation models. Compared to single imputation methods, this approach preserves the variability of the dataset and enhances the reliability of results. Multiple imputation will be performed using established statistical software (e.g., SPSS or R). Sensitivity analysis will also be conducted to assess the robustness of results under various assumptions regarding missing data. This comprehensive approach ensures the validity and reliability of research findings while maintaining statistical integrity throughout the analysis process and accounting for missing data. Qualitative interview audio files will be transcribed verbatim and anonymized, and analyzed using Grounded Theory with NVivo (Version 12, QRS International, Doncaster, Australia). Qualitative and quantitative data will be incorporated to better interpret the results across multiple stages during the trial.

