### Ensuring intervention compliance

2.8

To encourage subject compliance, we will (1) fully explain the subject’s responsibilities during the observation period at the time of recruitment and signing of the informed consent form. At the same time, we will strive to build strong relationships with participants with the aim of promoting mutual trust. (2) Throughout the study, researchers will provide short- and long-term self-care guidance and comprehensive health education after abortion. (3) The research team will assess the interaction between the intervention group and the system on a weekly basis. This is to ensure that participants are fully engaged. Regular monitoring can identify any issues or dropouts promptly, enabling the team to take corrective actions and maintain participant engagement.

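### Reconfirming and accompanying the T1 visit are written as intervention content only, so retention effort for the sole post-baseline PHQ-9 is unequal and differential loss is a risk

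*Protocol article*

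**What the plan says.** **Intervention arm.** Section 2.5.4 sets out the intervention by phase.

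- Phase 2 includes the instruction "Inform patients of follow-up appointment times, locations, procedures, required materials, and preparation requirements".
- Phase 3 includes "Contact the patient proactively before the follow-up examination to reconfirm the time, location, and examination items" and has the researcher stay with the patient throughout the visit.
- Phase 3 also lists, as a task of the attending doctor and researcher, guiding patients through the follow-up questionnaires.
- Section 2.8 adds: "The research team will assess the interaction between the intervention group and the system on a weekly basis". It says that this helps to find dropouts early.

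**Control arm.** Section 2.5.1 describes contact at enrolment only.

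**Not limited by arm.**

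- Section 2.1 has blinded medical staff tell patients the times and places of follow-up.
- Section 2.4.1 has follow-up arrangements explained at baseline and promises a gift at each survey.
- Section 2.8 has the subject's responsibilities explained at recruitment.
- Section 2.9 describes data collection: "In a standardized environment, investigators guide participants one-on-one to scan a QR code and complete a unified electronic questionnaire".

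**Outcome and analysis.** Table 1 shows PHQ-9 at T0 and T1 only. Section 2.7 plans GEE, multiple imputation, and sensitivity analyses under different missing-data assumptions. Section 2.3 raises 42 per group to 50 for loss to follow-up and gives no loss rate, overall or by arm.

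**The concern.** A reminder before the outcome visit and company on the day are typical ways of keeping participants in a trial. Here they belong to the treatment package, so the trial as written works harder to obtain the T1 score in one arm than in the other. The Background acknowledges that non-attendance occurs in this field: "Some patients refuse post-operative follow-up due to financial constraints".

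If more controls than intervention patients miss T1, and those who miss it differ in mood from those who attend, the observed groups are no longer the groups that were randomised. The primary comparison could then move in either direction. Because T1 is the only post-baseline assessment, there is no later or intermediate score to fall back on.

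**Working it through.** **1. Loss implied by the plan.** Section 2.3 gives 42 evaluable and 50 enrolled per group: (50 − 42)/50 = 16%, or 8 per arm and 16 of 100. No split by arm is stated.

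**2. The plan's own figure.** Inputs: "The test level α = 0.05 and test efficacy 1-β = 0.90 are set", "Two-sided tests will be used, with statistical significance set at p < 0.05" and "σ = 8, Δ = 5 in this example". The plan's formula gives (1.96 + 1.28)² × 2 × 8² / 5² = 10.4976 × 128 / 25 = 53.7, so 54 per group, not 42. The figure 42 is obtained with an SD of 7. This is a separate error. It matters here only because 42 evaluable per group at SD 8 gives about 82% power, so there is less room for loss than the plan suggests.

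**3. Effect of unequal loss on a completer comparison.** Let p be the share lost in an arm and g the mean T1 PHQ-9 of lost women minus that of retained women, taken as equal in both arms. The full-arm mean is the retained mean + p × g, so the retained mean is too low by p × g. The control-minus-intervention difference is therefore off by (p_control − p_intervention) × g.

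Keep the total at 16 lost of 100. The splits and g = 2 to 5 points are assumptions; the documents give neither.

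| Lost, intervention vs control | Difference in p | Shift, g = 2 | Shift, g = 5 |
|---|---|---|---|
| 8 vs 8 | 0 | 0 | 0 |
| 5 vs 11 | 0.22 − 0.10 = 0.12 | 0.24 | 0.60 |
| 4 vs 12 | 0.24 − 0.08 = 0.16 | 0.32 | 0.80 |
| 0 vs 16 | 0.32 − 0 = 0.32 | 0.64 | 1.60 |

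Against the target of 5 points, the 4 vs 12 row is 0.32/5 = 6% to 0.80/5 = 16%. In units of the stated SD of 8 it is 0.04 to 0.10. The extreme row is 13% to 32% of the target.

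**4. Direction.** If lost women are worse off than those retained (g > 0), the benefit is understated. If they are better off (g < 0), it is overstated by the same amount. The documents do not indicate which.

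**5. Power cost of the imbalance alone.** Normal approximation: power = Φ(5 / [8 × √(1/n₁ + 1/n₂)] − 1.96).

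- 42/42: Φ(2.864 − 1.96) = 82%
- 46/38: Φ(2.851 − 1.96) = 81%
- 50/34: Φ(2.812 − 1.96) = 80%

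The concern is bias, not power.

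**6. What imputation has to work with.** Table 1 lists no scale between T0 and T1. For a woman who misses T1, the psychological scores available are those from baseline. They can adjust for loss related to baseline mood, but not for loss that depends on how she feels at two weeks.

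**The case against.** Several stronger readings are tempting, and the documents do not support them.

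- **That the design makes unequal loss certain.** No figure shows or assumes more loss among controls. Gifts, the explanation of duties and notice of follow-up by blinded staff cover both arms and reduce the risk.
- **That the weekly monitoring in section 2.8 is one-armed tracking of T1.** It sits under intervention compliance and concerns use of the system, which controls do not have. It is mainly adherence monitoring and weak evidence here. The daily messages are likewise part of the treatment under test.
- **That the Background shows non-attendance among these participants.** The sentence is general and follows one on remote and underdeveloped areas. It does not describe consenting women at this hospital.
- **That the analysis relies only on imputation from baseline under missing at random.** Section 2.7 does not say so, and it plans sensitivity analyses under various assumptions.
- **That only one arm is helped with the questionnaire.** Section 2.9 describes one-on-one completion without limiting it to an arm. The difficulty is that Phase 3 also lists this help as intervention content, so the two sections need to be reconciled.

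It is also fair to say that a full protocol often holds reminder scripts, that the sizes above are assumed, and that they apply to completers rather than to the imputed analysis. An equal loss allowance per arm is conventional and no error.

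The asymmetry that the article itself states still stands. Reconfirmation and accompaniment are assigned to one arm as treatment content, which is more than a detail left out.

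**Conclusion.** The point holds as a risk. Followed as written, the plan puts more effort into obtaining the primary outcome in the intervention arm than in the control arm, at the only post-baseline assessment. Whether loss will differ, by how much and in which direction cannot be known from the documents.

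Under the assumed 4 versus 12 split and a gap of 2 to 5 points, completer bias is about 0.3 to 0.8 PHQ-9 points. That is modest against a target of 5 but not negligible. It rests on the implied 16% total loss and on the same gap in both arms. The planned imputation and sensitivity analyses may reduce the bias or bring it to light. They cannot remove it if attendance depends on unobserved mood at T1. Prevention is cheap, so the change is worth making.

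**What to change.** Take the T1 reminder and the completion of the T1 questionnaires out of section 2.5.4 and describe them as trial procedures. Use the same script, timing and number of contacts in both arms. The blinded medical staff who already give follow-up times should make the contacts, and the blinded investigators should collect the questionnaires. Align Phase 3 with sections 2.1 and 2.9 accordingly.

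If a Questionnaire Star link is sent to women who do not attend, apply the same rule and time window in both arms, record the mode of completion, and analyse the primary outcome with and without remote forms.

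The cost is about 50 extra reminders for each contact in the script, on channels and a platform already in use. The downside is that some forms are completed away from the standardised setting. If controls attend less often, remote forms will be more common in that arm, which is why mode must be recorded and the with-and-without comparison made.
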